**Methods:**

Our purpose here is to provide useful scientific information on the effect of pain-management group participation on chronic pain and pain-related co-morbidities and symptoms, as well as practical information for primary and occupational health services to initiate pain-management group activity.

This study will be carried out at primary care Occupational Health Helsinki (Helsinki city employees' occupational health services), with the Finnish Institute of Occupational Health as the research partner.

This is a stepped-wedge cluster randomized controlled trial among both male and female municipal employees aged 18 to 65, all of whom had visited an occupational doctor, nurse, psychologist, or physiotherapist because of any chronic pain unrelated to malignant disease. An additional inclusion criterion is work disability risk being elevated, based on a short screening questionnaire (modified Örebro questionnaire). Each participant and each interviewer will be blinded at randomization.

Three groups, 10 subjects in each, begin directly after recruitment with 6 weekly 2-h meetings and a follow-up meeting 6 months later. Three waiting-list groups begin 4 months later. Subjects complete self-administered questionnaires before and after the sixth meetings, also 6 months later. Primary outcomes are pain intensity, current work ability, pain self-efficacy, fear-avoidance beliefs, chronic pain acceptance, depressive symptoms, sleep problems, sickness absence days, and number of occupational health care contacts from OH's medical records.

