Sixth meeting:	• Themes of the meeting: new tools to improve pain management, making one's pain management plan • Filling out the follow-up inquiry • Discussion of homework and pain management tools. • Homework: The pain management plan will be given for writing at home
Seventh meeting, 6-month follow-up, Eighth meeting 12-month follow-up for ABC groups	• Themes of the meeting: psychological flexibility, importance of training and awareness skills, work as rehabilitation • Updating the pain management plan

Both participants and interviewers are blinded for the randomization, and at the end of the interview participants are randomized to one of the six groups (A, B, C, D, E, F). In this stepped-wedge design, every participant knows that he or she will receive an intervention, and the researchers know that no one will be left without treatment, which is not the case in conventional RCT [43].

The request for pain-management group activity originates with the patients themselves. Occupational Health Helsinki has provided three other kinds of groups during the previous 5 years (groups for sleep problems, depression, and burnout). The practical framework for our pain-management group is based on the feedback from those groups (size, facilities, timing, length, language, visual tools). After discussion between the leadership of the city of Helsinki and Occupational Health Helsinki, the results of this study will be provided to the participants in the form of the result report (via e-mail) as well as articles in the media (OHC website, Twitter and such).

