### Timetable

2.5

Recruitment lasts for 1 month, with the Screening (Scr) Questionnaire (modified Örebro questionnaire), filled out before the interview and during the interview. ABC groups start their six meetings one month after recruitment ends. The before (Bef)1 questionnaire is completed during the interview and returned at the first meeting. The After (Aft) questionnaire is filled out during the sixth meeting. DEF groups are on the waiting list and get their Bef1 questionnaire by mail, while the first three groups (ABC) are in the intervention. Bef1 is returned in one week. DEF start the intervention, six meetings 4 months after the first intervention. The Bef2 questionnaire is sent by mail to the DEF groups before intervention and collected on the first meeting day. The Aft questionnaire is completed at the end of the sixth meeting, and participants are advised to book time for their own occupational health nurse if a group member wishes support in completing the pain management plan. Aft6m is filled out at the 6-month meeting. The Aft12 m is completed in the meeting 12 months after intervention; the Aft12 m meeting is arranged only for the ABC groups (Fig. 2).

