### Intervention

2.6

The pain management groups are led by occupational health professionals (Helsinki city's OH personnel) who voluntarily participate in this study. The group leaders are experienced group tutors, and they will have mastered the biopsychosocial and cognitive approach. An experienced pain psychologist is hired as a mentor for the group tutors. The group meetings are once a week, after work, lasting 2 h with a 15-min coffee break for 6 weeks. During the intervention, participants will read some chapters from the book *Ota kipu haltuun* (Rethinking pain) by [name], as homework [44] (Table 1). The follow-up meeting is 6 months after the sixth meeting. The second follow-up meeting is 12 months after the sixth meeting, only for A, B, and C groups. The content of the meetings is in Table 1.

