The content of the baseline and of the follow-up questionnaires is, to a large extent, the same. They contain the same 10 questions from the screening questionnaire, as well as questions on pain-related fear, pain self-efficacy, chronic pain acceptance, self-rated work ability, the number of sick-leave days due to any reason and due to pain, medication use for pain and for other purposes, non-pharmaceutical treatments in use, feeling energized, enjoying life, physical exercise, smoking, body weight and height, and chronic diseases. Sickness-absence data and use of occupational health services is collected from the OHS patient register 6 months before and 6 months after intervention.

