### Outcomes

2.8

Outcomes, variables, and covariates are listed in Table 2.

Outcomes are pain intensity, current work ability, pain self-efficacy, pain-related fear avoidance beliefs, chronic pain acceptance, depressive symptoms, sleep problems, sickness absence days and number of occupational health care contacts which are collected from OH's medical records.

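### Nurse visits prompted by the course fall in the after window of the occupational health contacts outcome, and the count does not separate them from other care-seeking

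*Protocol article*

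**What the plan says.** Four parts of the protocol article bear on this.

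- **The plan.** Table 1 lists as homework from the sixth meeting: "The pain management plan will be given for writing at home". Section 2.5 (Timetable) adds that "participants are advised to book time for their own occupational health nurse if a group member wishes support in completing the pain management plan".
- **The outcome.** Section 2.8 names as an outcome the "number of occupational health care contacts which are collected from OH's medical records". The abstract places it among the primary outcomes. The aim at the end of the Introduction includes use of health services.
- **The window.** Section 2.7 states: "Sickness-absence data and use of occupational health services is collected from the OHS patient register 6 months before and 6 months after intervention". Table 2 gives the same window and does not restrict the count by type of contact or reason for it.
- **The comparison.** Section 2.11 compares the post-intervention period with the pre-intervention (control) period.

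Section 2.3 says that participants keep their usual access to OH services during the study. Nothing in the article marks, excludes or separately reports visits made for the plan.

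**The concern.** The contacts outcome is meant to show whether the course changes how much participants use OH services. The rationale leads one to expect a fall: the Introduction cites less use of health services after cognitive-behavioural therapy, and the Discussion cites fewer physician visits.

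The course also offers a reason for a new kind of contact. A nurse visit for help with the plan cannot happen before the plan is handed out, so it can add to the after count only. Waiting-list participants have no plan yet, so randomization does not balance these visits. A mixed model cannot remove them either, because the register total does not identify them. If uptake is appreciable, a real fall in other care-seeking would look smaller than it is.

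**Working it through.** The article states no figure for this outcome, so there is nothing to reproduce. The check has three parts.

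**1. Timing.** The plan is handed out at the sixth meeting, the last weekly one. Support visits come after that. The article does not give the exact day on which the after window opens, but no plausible start would leave these visits out as a group. The before window cannot contain any.

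**2. Size of the after-window addition.** The article gives neither uptake nor baseline rate, so the following are assumptions:

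- b = mean contacts per participant in the 6 months before: 4, with 2 and 8 as a range
- true fall in other contacts: 20%
- s = share of participants who book one extra plan visit: 0.10, 0.50 and, as an extreme, 1.00

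Observed change = (0.8b + s − b) / b = −20% + s/b.

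| b | s = 0.10 | s = 0.50 | s = 1.00 |
|---|---|---|---|
| 2 | −15% | +5% | +30% |
| 4 | −17.5% | −7.5% | +5% |
| 8 | −18.75% | −13.75% | −7.5% |

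For b = 4, the after mean is 0.8 × 4 = 3.2 without plan visits. With s = 0.10 it is 3.3, and 3.3/4 − 1 = −17.5%. With s = 0.50 it is 3.7, and 3.7/4 − 1 = −7.5%. Among 60 participants these are 0.10 × 60 = 6 and 0.50 × 60 = 30 added contacts.

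The formula treats every plan visit as extra. If some replace a visit that would have happened anyway, or are combined with one, the true addition is smaller than s.

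**3. What may sit in the before window.** Participants are recruited by OH staff and then interviewed individually (section 2.3). For groups A to C the interview falls inside the 6 months before the course. Recruitment lasts 1 month and the course starts one month after it ends (section 2.5), so the gap is about 1 to 2 months. For groups D to F it is about 4 months longer, 5 to 6 months, if the wait runs from the start of the first courses, which puts the interview near the edge of the window.

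The article does not say whether these contacts are entered in the register. If a share r of participants has one such recorded contact before:

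Observed change = (0.8b + s) / (b + r) − 1.

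With b = 4 and s = 0.50:

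- r = 0: 3.7/4.0 − 1 = −7.5%
- r = 0.50: 3.7/4.5 − 1 = −17.8%
- r = 1.00: 3.7/5.0 − 1 = −26%

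The net error can therefore understate the assumed 20% fall or overstate it.

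**The case against.** Several points on the other side stand.

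- **The visit is optional.** The advice applies only to those who want help. Nothing is scheduled or required, and section 2.6 does not list the visit as part of the intervention. A reader might infer that the course sends everyone to the nurse; the text does not say so, and uptake may be small.
- **Total use is a legitimate quantity.** The stated aim is use of health services. A visit that the course prompts is a real consequence of the course, and a service deciding whether to run such groups would want it counted. A reader might conclude that the aim cannot be answered at all. That does not follow: the total answers one reasonable question, and only the narrower one, whether care-seeking itself changed, is blurred.
- **The net direction is not fixed.** A reader might infer that the bias must run against the course. Recorded recruitment or interview contacts would push the other way.
- **Group meetings.** A reader might also infer, because "The pain management groups are led by occupational health professionals (Helsinki city's OH personnel"), that the sessions themselves count as contacts. Nothing shows that they are entered in the register, and the 6-month meeting lies at the edge of the window.
- **Marking is not neutral.** Nurses who label visits know that the participant has had the course. Removing labelled visits from the outcome could favour the course, which argues against redefining it.
- **A full protocol may deal with this.** The article is condensed, and an exclusion could exist elsewhere. However, the article fixes the outcome, its source and its window, and also states the advice that feeds it. The overlap comes from what is stated, not only from silence.

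**Conclusion.** The concern holds in a limited form. A type of visit that can exist only after the course can enter the after count of an outcome that the abstract calls primary, and the article does not separate it from other contacts. The unclassified count may partly mask a fall in contacts.

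The size cannot be determined from the article. On the assumptions of 4 contacts before and a true 20% fall, the distortion is small at 10% uptake and removes more than half of the fall at 50% uptake. Both results rest on invented inputs, and contacts before the course could offset them. The documents do not support saying that the outcome is invalid, or that a null result on contacts would necessarily hide a benefit. What they support is that the total alone cannot show whether care-seeking changed apart from the visits that the study generated.

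**What to change.** Keep total OH contacts as the stated outcome, and leave the advice to participants as it is. Before data are seen, add to the outcome definition:

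1. Study-generated contacts are marked by visit reason in both windows: the study interview, any group meetings that are recorded in the register, and nurse visits booked for the plan.
2. Contacts are reported with and without the marked ones, as a prespecified sensitivity analysis.
3. Physician contacts are reported separately from nurse contacts. The cited evidence concerns physician visits, and this split does not depend on the marking.
4. A visit that combines plan support with pain care follows a fixed rule, for example that it counts as an ordinary contact.

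The cost is a few sentences and a visit-reason mark at booking. The marking has to be in place before the visits occur, because unmarked plan visits may not be identifiable later. The small downside is that mixed visits need classifying by nurses who are not blind to the course. Keeping the total as the outcome, and the split as a sensitivity analysis, limits the harm from that.

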**Fig. 2 fig2:**
[figure not shown]
Timetable for the intervention.

### Intervention

2.6

The pain management groups are led by occupational health professionals (Helsinki city's OH personnel) who voluntarily participate in this study. The group leaders are experienced group tutors, and they will have mastered the biopsychosocial and cognitive approach. An experienced pain psychologist is hired as a mentor for the group tutors. The group meetings are once a week, after work, lasting 2 h with a 15-min coffee break for 6 weeks. During the intervention, participants will read some chapters from the book *Ota kipu haltuun* (Rethinking pain) by [name], as homework [44] (Table 1). The follow-up meeting is 6 months after the sixth meeting. The second follow-up meeting is 12 months after the sixth meeting, only for A, B, and C groups. The content of the meetings is in Table 1.

### Data collection

2.7

Data collection can be seen in Table 2. Variables. During the recruitment, a short screening questionnaire (Scr), a slightly modified version of the validated Örebro Short Questionnaire is filled out [45]. A question as to the pain lasting more than 3 months is not calculated, it is one of the inclusion criteria. The sum score is calculated based on 10 questions, each earning 0–10 points: pain areas, (head, neck-trapezius, shoulder/upper arm, elbow or lower arm, wrist/hand, upper back, lower back, hip/thigh, knee/shin, ankle/foot-pain), pain intensity, anxiety, depressive symptoms, being able to do light work for an hour, sleep, expected risk of pain remaining persistent, self-perceived ability to work within the next 3 months, two items on fear-avoidance: “I should stop what I am doing until the pain decreases” and “I should not do normal activities or work when I feel pain”. Maximum sum is 100 points.

**Table 2 tbl2:** Variables.

Variables		Questionnaires			
		Scr	Bef1, Bef2	Aft	Aft 6 m, Aft 12 m
*Outcomes*					
	Pain intensity, 1 item (0 = no pain, 10 = the worst possible pain)	x	x	x	x
	Current work ability, 1 item (0 = totally disabled, 10 = the ability to work at its best)		x	x	x
	Pain self-efficacy, 10 items (0 = not at all confident, 6 = completely confident)		x	x	x
	Chronic pain acceptance, 8 items (0 = totally disagree, 6 = totally agree)		x	x	x
	Depressive symptoms, 1 item (0 = not at all, 10 = extremely much)	x	x	x	x
	Sleep problems, I can sleep at night (0 = I can do it despite pain, 10 = I can't do it because of the pain problem)	x	x	x	x
	Sleep problems, days slept well during the past week (0–7)		x	x	x
	Sickness-absence days (6 months before and after intervention)				
	Health care contacts, number of contacts (6 months before and after intervention)				
*Pain-related variables*	Pain areas, 10 areas (0 = no, 1 = yes)	x	x	x	x
	Pain-related fear-avoidance, 2 items (0 = totally disagree, 10 = totally agree)	x	x	x	x
	Fear of movement, 3 items (0 = totally disagree, 6 = totally agree)		x	x	x
	Self-perceived risk of current pain becoming persistent (0 = no risk, 10 = very large) risk)	x	x	x	x
	Use of painkillers during the previous week, 3 items (0 = none, 1 = few times a week, 2 = every day) Anti-inflammatory drug or Paracetamol Strong analgesic, opiate, medications for chronic pain		x	x	x
	Other medication (open question)		x	x	x
	Non-pharmaceutical pain management tools (open question)		x	x	x
*Work ability variables*	Current ability to do light work for an hour (0 = can do despite pain, 10 = can't do at all because of pain)	x	x	x	x
	Self-estimated work ability in 3 months, 2 items (0 = very large chance, 10 = no chance)	x	x	x	x
	Sickness-absence days during the past 30 days (0–30)		x	x	x
	Sickness-absence days for pain during the past 30 days (0–30)		x	x	x
*Other*	Days enjoying life during the past week (0–7)		x	x	x
	Days feeling active and energetic during the past week (0–7)		x	x	x
	Days feeling tense or restless during the past week (0–7)		x	x	x
*Covariates*	Age	x			
	Gender	x			
	Occupational title		x		
	Height		x	x	x
	Weight		x	x	x
	Physical exercise, number of times per week		x	x	x
	Kind of sport/sports, open question		x	x	x
	Chronic disease, (0 = no, 1 = yes)		x	x	x
	Chronic disease, if yes, which, open question		x	x	x
	Smoking, (0 = no, 1 = no, quit, 2 = yes)		x	x	x
	Quit smoking, years smoked		x	x	x
*Benefits of*	Usefulness of mindfulness practice (0 = not at all useful, 10 = very useful)			x	
	Usefulness of peer group for different issues, 17 items (0 = not at all helpful, 6 = very helpful)			x	
	Ranking importance of features of peer group (1 = most helpful, 2 = next most helpful, etc.) 5 items			x	
	Benefit from participating in pain- management group (0 = not at all useful, 10 = very useful)				x

After the recruitment and interview, the baseline questionnaire (Bef1) is completed or subjects are given a 1-week response time. The waiting-list group fill out an additional questionnaire during the waiting-list period (Bef2). After intervention, the first follow-up questionnaire (Aft) is filled out, and the second follow-up questionnaire (Aft6m) at the 6-month follow-up group meeting (seventh meeting). The third follow-up questionnaire (Aft12 m) is sent via mail only for the first intervention group.

The content of the baseline and of the follow-up questionnaires is, to a large extent, the same. They contain the same 10 questions from the screening questionnaire, as well as questions on pain-related fear, pain self-efficacy, chronic pain acceptance, self-rated work ability, the number of sick-leave days due to any reason and due to pain, medication use for pain and for other purposes, non-pharmaceutical treatments in use, feeling energized, enjoying life, physical exercise, smoking, body weight and height, and chronic diseases. Sickness-absence data and use of occupational health services is collected from the OHS patient register 6 months before and 6 months after intervention.

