### Participants and recruitment

2.1

The study base comprises the employees of the city of Helsinki, the country's largest employer. The city of Helsinki has its own occupational health services (OHS), which provides OH services for more than 40 000 employees in 800 occupations of 30 industrial fields. The average age of employees in the city of Helsinki in 2014 was 46, the largest age-group in the city being 50–59. The youngest employees were 19 years old and the oldest employees of the city of Helsinki were 65 [37]. We therefore decide to include employees aged 18–65 years. Systematic review stated that most often the exclusion criteria's were psychological conditions, malignancy, recent or scheduled surgery, pregnancy and trauma [38]. Consistently we will exclude severe diseases such as malignancies, which would lead possibly to missed meetings and lost follow-up, and also we exclude a disease such as severe mental illness, which could bias results [39].

Inclusion criteria•18- to 65-year-old Helsinki city employee•Chronic pain (lasting) for 3 months or longer•Suitable for group activity, by being willing to share own thoughts with other group members•Work disability risk being elevated, based on a short screening questionnaire (modified Örebro questionnaire). Screening survey points for work disability ≥50/100

Exclusion criteria•Malignant disease such as cancer or severe mental disease•Participating in another pain-management group•Experiencing a major psychological or physical life crisis•Being at no elevated risk for work disability, Screening survey (modified Örebro questionnaire) points <50/100

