### Statistical analysis

2.11

The post-intervention period is compared with the pre-intervention (control) period. Linear mixed-effect models allow analysis of repeated measures data and the differences in the outcomes of interest between intervention and control periods. Intention-to-treat analyses are conducted, and time-effect and intra-cluster correlation coefficients reported. When the null hypothesis (i.e., no difference) is rejected, it is always possible to conclude, whatever the results of the study are, that there exists a difference but actually there is not (type-I error or false positive) [51]. Since the sample size is rather small, exact confidence interval for outcomes will be the choice to avoid statistical bias and false-positive or false-negative errors [51].

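### As 6-month totals before and after each participant's own intervention, sickness-absence days and health-care contacts give no randomised contrast, and the recruiting visit may inflate the before-count of contacts

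*Protocol article*

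**What the plan says.** The abstract lists among the primary outcomes "sickness absence days, and number of occupational health care contacts from OH's medical records". Data collection (2.7) sets the window: "Sickness-absence data and use of occupational health services is collected from the OHS patient register 6 months before and 6 months after intervention". Table 2 repeats it for each outcome: "Sickness-absence days (6 months before and after intervention" and "Health care contacts, number of contacts (6 months before and after intervention". Neither row has a tick at any questionnaire time point, so the register windows are the only definition given. Statistical analysis (2.11) compares the period after the intervention with the period before it, calls the latter the control, and says a time effect will be reported.

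On entry, the abstract describes the participants as people "all of whom had visited an occupational doctor, nurse, psychologist, or physiotherapist because of any chronic pain unrelated to malignant disease", and Participants and recruitment (2.1) requires "Screening survey points for work disability ≥50/100".

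On timing, Study design (2.4) starts groups A, B and C within 1 to 3 weeks of recruitment. Timetable (2.5) starts them one month after a one-month recruitment ends. Both give groups D, E and F a wait of about 4 months, but neither says clearly whether it runs from the start or the end of the first groups' meetings. Timetable (2.5) adds that, after the sixth meeting, "participants are advised to book time for their own occupational health nurse if a group member wishes support in completing the pain management plan".

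**The concern.** A stepped-wedge trial draws its randomised information from clusters that are untreated while others are treated, at the same calendar time. Windows that travel with each participant's own intervention do not line up in calendar time. A before/after difference in totals then mixes the effect of the groups with season, any drift in service use, and the fall expected when people are selected at a bad time and followed.

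Sickness absence and service use are stated aims in the Introduction and carry the service argument. A fall in contacts could be reported as a benefit of the programme and used to support the larger multicentre study mentioned under Limitation, although randomisation had contributed nothing to it.

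**Working it through.** The protocol gives no sample-size or effect figure for the register outcomes. Its 10 per group and 60 in total were derived for pain intensity, so there is no plan figure to reproduce here.

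**1. Where the windows lie.** Month 0 is the first ABC meeting. Six weekly meetings span 5 weeks (first to sixth) or 6 weeks (whole programme): 5/4.345 = 1.15 and 6/4.345 = 1.38 months.

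| Window | Wait counted from ABC start | Wait counted from ABC end |
|---|---|---|
| ABC before | −6 to 0 | −6 to 0 |
| ABC after | 1.15 to 7.15, or 1.38 to 7.38 | same |
| DEF first meeting | 4 | 5.15 or 5.38 |
| DEF before | −2 to 4 | −0.85 to 5.15, or −0.62 to 5.38 |

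**2. Shared time.** The overlap of ABC after with DEF before is:
- wait from ABC start: 4 − 1.38 = 2.62 to 4 − 1.15 = 2.85 months, which is 44% to 47% of 6 months;
- wait from ABC end: 5.15 − 1.15 = 4.00 months, which is 67%.

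No reading reaches 6 months.

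**3. What totals can identify.** With one before and one after total per person there are four cells: ABC before, ABC after, DEF before, DEF after. The treatment indicator is (0, 1, 0, 1).
- With a before and an after effect, the design matrix has rank 2, and still rank 2 when treatment is added. The after column is the treatment column.
- With a separate effect for each of the four calendar windows, the rank is 4, and still 4 with treatment.

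Treatment is not separable from time in either case unless a parametric time trend is assumed.

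**4. The two before-windows differ in kind.** On the Timetable (2.5) dates, recruitment runs from month −2 to −1. ABC's before-window then has 4 of its 6 months ahead of recruitment. DEF's has none: 5 of 6 months (wait from ABC start) or all 6 (wait from ABC end) follow recruitment. Selection on a visit and on a score of at least 50 therefore bears on the two arms' before-totals differently.

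**5. Whether the recruiting visit is counted (contacts only).** The recruitment month lies wholly inside ABC's before-window. For DEF:
- wait from ABC start: the window opens at −2, so the recruitment month is wholly inside;
- wait from ABC end: if recruitment ends g months before ABC starts, it runs from −(g + 1) to −g, and the share inside is max(0, opening − g), with opening 0.85 or 0.62. For g = 1 the share is 0. For g = 3 weeks (0.69) it is 0.16 or 0. For g = 1 week (0.23) it is 0.62 or 0.39.

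**6. How much it could matter.** Contact rates are not in the protocol; assume λ = 2 to 6 per half-year.
- Upper case: everyone is sampled at a visit that lies in the window, on top of the usual rate. Apparent fall = 1/(λ + 1): 1/3 = 33% at λ = 2 and 1/7 = 14% at λ = 6.
- Lower case: entry only requires at least one contact somewhere in the window (zero-truncated Poisson). Before-mean = λ/(1 − e^−λ), so apparent fall = e^−λ: 14% at λ = 2 and 0.2% at λ = 6.

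A simulation of 60 people with no true effect used gamma-Poisson counts with mean 2 to 6 (3 to 12 among people recruited at a visit) and a paired test. It rejected in about 35% to 87% of trials if every before-window held one extra entry visit, 13% to 34% if half did, and 4% to 5% if none did.

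**The case against.** The best reply is that control time exists. ABC's after-window and DEF's before-window overlap, a time effect is planned, and Data collection (2.7) does not say that the register data are reduced to one figure per window. A reader might infer from the moving windows that there is no same-time control at all. The documents do not support that: step 2 shows 2.6 to 4.0 shared months. What stands against the reply is that Table 2 defines the outcomes only by the two 6-month windows, and that totals over those windows leave the overlap unused.

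A reader might also infer that both outcomes must shift by construction. That is not supported. The recruiting visit and the suggested nurse bookings touch contacts, not absence days. The abstract sets no date limit on the qualifying visit, and for DEF its inclusion depends on how the wait is counted. The nurse bookings are optional, and they are real service use caused by the programme, which the stated aim covers. Removing them would take contacts away from treated people only.

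Finally, because "Linear mixed-effect models allow analysis of repeated measures data" is the only modelling statement, a reader might conclude that skewed counts will get wrong intervals. That sentence is general, the same section mentions exact intervals, and a model for counts may be set in an analysis plan that is not shown. It is not part of this point.

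**Conclusion.** The point holds for the design of the two register outcomes. As 6-month totals they are uncontrolled before/after figures, with treatment confounded with calendar time and with regression to the mean. A later choice of model could not recover a randomised contrast from such totals; dated records are needed. This rests on the stated windows and the wait of about 4 months, and on reading the outcomes as totals, which is how Table 2 labels them.

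For contacts there is a further, conditional bias: the recruiting visit probably falls in ABC's before-window, and falls in DEF's wholly, partly or not at all according to the timetable reading. Its size rests on assumed rates. The range from near 0% to 33% is what those assumptions allow, with 33% the upper case; the false-positive rates above are likewise illustrations, not predictions.

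**What to change.** - Extract dated absence and contact records for all participants over one common calendar span.
- Make the main register comparison ABC versus DEF over the shared waiting months, from ABC's sixth meeting to DEF's first. Adjust for the count in a fixed period before recruitment and allow for clustering by group.
- Leave the recruiting visit and the study interview out of the counts in both arms.
- Keep visits prompted by the programme, such as pain-plan bookings, in the main count, and also show them separately.
- Report the 6-month before and after figures as descriptive.
- Reconcile Study design (2.4) with Timetable (2.5) on when ABC starts and from which point the 4-month wait is counted, so that every window has fixed dates.

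The cost is adding dates to an extract that is already planned. The price is a main window of about 2.6 to 4.0 months instead of 6, so fewer events per person and less precision.
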